### Recruitment, eligibility and randomization

Participants enrolled in the trial were recruited from two sources, a program providing short-term in-home support for individuals who are medically comprised (referred to as the In-Home Support Program; IHSP) or the community at-large. IHSP provides homebound elders assistance regaining independence after illness or hospitalization through home health and homemaker services, home delivered meals, transportation, or companions but does not typically involve formal and systematic depression screening. Recruitment from IHSP involved integrating depression screening in the assessment process of participants in the program. Recruitment to the community at-large involved print media, presentations to community groups, and print media.

Eligibility criteria for BTB include being African American; ≥ 55 years of age; English speaking; cognitively intact (MMSE > 24), and a score ≥ 5 on the PHQ-9 on two sequential testing occasions. Other criteria are practical and include having a home telephone and planning to live in the area for 8 months. Individuals are not eligible with serious mental illness histories, life-limiting illnesses, involvement in another clinical depression trial, or if living in assisted living or nursing home facilities. Individuals receiving anti-depressant medications or other mental health treatments are eligible.

As individuals from IHSP may be more medically and functionally compromised than those enrolled from the community at-large, we used a stratified randomized design to assure equivalence between groups along this dimension. Permuted block randomization with each stratum (IHSP versus other recruitment source) to control for possible changes over time in subject mix was employed. The blocking number was developed by the trial senior statistician and was not disclosed to the investigative team.

### Measures

In selecting measures for this study, we chose those with known reliability and validity; sensitivity to change that is expected to occur as a consequence of intervention; relevance to and wide usage in depression research, and acceptability by the target population. Our primary outcome measure is the Patient Health Questionnaire (PHQ-9), a brief, 9-item self-report measure specifically developed as an assessment tool for the diagnosis of depression in primary care. In addition to its psychometric soundness and demonstrated reliability, validity, sensitivity and specificity, the measure is also widely used in community-based settings and research trials. It yields a depression severity score (0 to 27) and a diagnostic category (minimal to none, mild, moderate, moderate severe, severe) mapping on to the 9 DSM-IV. Administration involves initially asking two items (loss of interest; feeling upset, distressed or depressed). Individuals reporting that either symptom occurs more than half the time over past two weeks are administered 7 other items [29]. Thus, two scores can be derived: symptom severity and categorical diagnosis. We also consider as a complementary secondary outcome a change in categorical diagnoses in which we seek to determine the number of persons who shift to none to minimal diagnostic category at 4 months. A categorical approach provides a clinical interpretation of treatment efficacy and also whether the intervention addresses certain syndromes better than others (e.g., minor depressive disorder may be more responsive to the proposed intervention than major severe depression). While the PHQ-9 is a self-report measure, self-report has been shown to be highly associated with clinical determinations. Also, the measure has been shown to be effective when administered in person or via telephone. The secondary outcome measures for the trial are presented in Table 1.

**Table 1 T1:** Secondary Outcome Measures for BTB Trial

Domain	Description of Measure	# of Items
Functional difficulties	Level of difficulty (1 no difficulty to 5 unable to do due to health problem) with items reflecting ambulation, self-care and instrumental activities of daily living [31].	18
Depression knowledge	Self-efficacy concerning ability to recognize and treat depression rated from absolutely confident (4) to not confident at all (1) [32].	10
Behavioral Activation	Behavioral Activation Scale (Abbreviated) contains items rated on a scale from 0 not at all to 6 completely and address activation in a range of daily activities (e.g., stayed in bed too long; I accomplished the goals I set out to do to) [33].	26
Anxiety	State Anxiety Scale in which items are endorsed as 1 (very much) to 4 (not at all) [34].	10
Quality of daily life	Adapted from the Perceived Change Index, items reflect mood, sleep quality and daily well-being rated from 1 (gotten much worse in past month) to stayed the same (3) to improved a lot (5) [35].	14
Overall quality of life	Adapted from the Quality of life for Alzheimer's Disease items are assessed from 1 (poor) to 4 (excellent) concerning experience of pleasure, hopefulness, positive relationships with family and friends [36].	12

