### Aims and study hypotheses

Our primary aim is to test the immediate effect of the intervention at 4-months on symptom severity (PHQ-9 severity score) in African American older adults (primary trial outcome; between group comparison). Our hypothesis is that participants in the initial treatment group will report fewer depressive symptoms in comparison to control group participants receiving usual care. We also seek to test the maintenance effect of the intervention at 8-months on depression (within group comparison). Our hypothesis is that participants in the initial treatment group will maintain reduced symptom presentation from 4 to 8 months and the wait-list control group will show similar reductions in depressive symptoms as the initial treatment group (within group comparison).

A secondary aim is to evaluate whether BTB has immediate (4 months) and long-term (8 months) effects on quality of life indicators, functional difficulty, anxiety, and depression education and behavioral activation levels. We expect that the initial treatment group will show improvements in these areas relative to the wait-list control group, that improvements will be maintained at 8 months and that the wait-list control group will demonstrate similar improvements at 8 months following their receipt of the intervention.

Several exploratory aims are also proposed. We will evaluate the mechanism of action, or pathways, by which treatment gains are obtained. Given that behavioral activation represents conceptually the key active ingredient of the proposed intervention, we plan to evaluate its mediational effect. We will also evaluate whether the intervention has a differential treatment effect based on a study participant's gender, age, and living arrangement (alone or with others). Given that previous research suggests that participant characteristics may moderate depressive symptoms and treatment outcomes, these exploratory analyses will provide insight as to whether this particular treatment benefits some groups more than others.

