The focus of the primary analysis is to examine the effect of the intervention on symptom severity based on the principle of "intention to treat." That is, all subjects assigned to the initial treatment group will be part of the primary analyses regardless of the actual number of intervention contacts received. This approach tests the effects of the intervention without accounting for the extent to which study participants actually receive the intervention. It effectively penalizes the intervention if subjects are not willing to receive it or if subjects receive different doses or exposure to treatment. We will calculate adjusted mean differences in treatment effects on the outcome measure at 4-months using analysis of covariance. We will include as covariates the baseline value of the outcome measure and the stratification variable (recruitment source). Other background characteristics may also be used as covariates if large or statistically significant differences between initial treatment and wait-list control group participants are found for those variables in analyses conducted prior to any efficacy analyses. Prior to conducting the ANCOVA, we will test the normality assumption for the dependent measure by examining the distribution of the residuals. If the residual distribution is skewed, we will use a transformation of the data.

For purposes of reporting results, we will also compute proportions improved. We will use two definitions of improvement: any reduction in PHQ-9; a reduction sufficient to move the patient at least one severity category lower. Note that we do not have to worry about the no symptom (0-4) at baseline group in this definition, as that group is not eligible. The comparison of treatment to wait-list control will be with odds ratio and 95% confidence intervals. We will also examine clinical significance by conducting subsidiary analyses that examine the proportion of individuals in treatment compared to controls who change diagnostic categories. Finally, in another set of analyses we will incorporate measures of the extent to which treatment has been received to evaluate relationship of dose/intensity to treatment outcome. This is for reporting purposes and we are not powering for these alternative endpoints.

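### The PHQ-9 is described as skipping seven items for anyone below a two-item gate, which contradicts the 0 to 27 score used as the primary outcome

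*Protocol article*

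**What the plan says.** The Aims section makes the PHQ-9 severity score at 4 months the primary outcome, compared between groups. The Measures section describes the instrument as "a brief, 9-item self-report measure specifically developed as an assessment tool for the diagnosis of depression in primary care" and says of it: "It yields a depression severity score (0 to 27) and a diagnostic category".

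The same paragraph then sets out how it is given. Two core items come first, on loss of interest and on low mood. The rule for the rest is: "Individuals reporting that either symptom occurs more than half the time over past two weeks are administered 7 other items". The next sentence presents symptom severity and categorical diagnosis as the two scores that follow from this.

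The score and its bands are used widely:
- The primary ANCOVA takes the 4-month score, adjusted for baseline and recruitment source (Analytic plan).
- A complementary secondary outcome is the "number of persons who shift to none to minimal diagnostic category at 4 months" (Measures).
- One of the two definitions of improvement is "a reduction sufficient to move the patient at least one severity category lower"; the other is any reduction in the score (Analytic plan).
- The 4-to-8-month retention analysis, the mediation regressions and the cost per reduction in symptoms use the same measure.

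The article does not confine the gate to screening, does not exempt the follow-up interviews, and gives no scoring rule for items that were not asked.

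**The concern.** A severity total over nine items exists only if nine items are asked. Under the stated rule, a participant whose two core symptoms are both below the gate is never asked the other seven. That participant's score then reflects the skip rule more than the remaining symptoms.

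Follow-up is the sensitive point. Entry requires a score of at least 5 on two occasions. With unasked items at zero, nobody below the gate can reach 5, so everyone enrolled must have passed the gate at both screens. Falling below it at 4 or 8 months would then register as a large improvement and as a move to the none/minimal band, even if other symptoms persist.

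At stake are the only primary endpoint, the categorical outcomes that give it clinical meaning, and the retention analysis.

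**Working it through.** **Inputs from the article.** Nine items; range 0 to 27; two gate items and seven others; gate at more than half the time; bands 0-4, 5-9, 10-14, 15-19 and 20 or more (Table 3); entry at 5 or more.

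**Assumptions.** Items are scored 0 to 3, inferred from 27 / 9 = 3. More than half the time means an item score of 2 or more.

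**1. Stated range.** 9 × 3 = 27. The range of 0 to 27 is reproduced, but only when all nine items are asked.

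**2. Below the gate, unasked items counted as 0.** Each core item is 0 or 1, so the total is 0 to 1 + 1 = 2. With all nine items asked, the same person could score up to 2 + 7 × 3 = 23, which reaches the severe band. Example: a score of 1 on every item gives 9 (mild) on nine items and 2 (none/minimal) under the gate.

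**3. Gate read as item score 3.** Each core item is 0 to 2, so the gated total is 0 to 4, still wholly inside the 0-4 band. The nine-item total could reach 4 + 21 = 25.

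**4. Unasked items treated as missing.** A person below the gate has two of nine items and no severity score, so the primary ANCOVA has no outcome value for them.

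**5. The jump at the gate.** Let the core items go from (2, 0) to (1, 0), with the other seven unchanged and summing to S, where S is 0 to 21. The nine-item score falls by 1. The gated, zero-scored total falls from 2 + S to 1, a drop of 1 + S, or 1 to 22 points.

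**6. Who is misbanded.** Above the gate all nine items are asked and the band is correct. Below it, the band is wrong only for people whose nine-item total would be 5 or more. Zero-scoring can only lower a score, so the share in the 0-4 band at follow-up is overstated wherever such people exist and is never understated.

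**7. Effect on the treatment comparison.** This is illustrative only; no input comes from the trial. The model is one-factor with ordinal items: loading 0.7, thresholds -0.2, 0.6 and 1.3, 400,000 per arm, unasked items at 0. Shifts are on the latent item scale.

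| Latent shift, core / other items | Standardised effect, nine items | Standardised effect, gated |
|---|---|---|
| 0.3 / 0.3 | 0.38 | 0.31 |
| 0.5 / 0.2 | 0.34 | 0.40 |
| 0.8 / 0.1 | 0.30 | 0.57 |

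The gate dilutes the effect when treatment moves all items equally and inflates it when treatment acts mainly on the two core items. A rerun agreed to within about 0.01.

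**The case against.** The strongest reply is that the sentence loosely describes a screening or diagnostic step. It sits in a general account of the instrument and carries a citation. The sections on the follow-up interviews and the analysis mention no gate, and the same paragraph calls the measure nine-item with a 0 to 27 range. All nine items may have been asked throughout. The article cannot exclude this, so corrupted 4-month data are not shown. But the paragraph does derive the outcome scores from the gated administration, so as written the gate governs the primary outcome. Even on the benign reading the text needs correcting.

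A second reply is that scoring unasked items as zero is an assumption and that scoring rules often sit in a fuller document. That is fair, and zero-scoring should not be reported as the trial's practice. It does not remove the problem, because the alternative leaves those participants without a score.

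A reader might also infer that the gate lowers power, biases the effect in a known direction, or makes the bands wrong in general. The documents support none of these. The direction depends on which items treatment moves. Behavioral activation aims to restore pleasurable activity, so a larger effect on the core items, and hence exaggeration, is as open as dilution. Misbanding is limited to the group in step 6, whose size is not given.

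**Conclusion.** The stated administration contradicts the stated 0 to 27 primary score. Followed as written, it gives participants below the gate either a total confined to 0-2 (0-4 if the gate is an item score of 3) or no valid nine-item score.

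For an individual, the understatement is up to 21 points, the seven unasked items at 3 each. If unasked items are zero-scored, anyone below the gate with a nine-item total of 5 or more is wrongly classed as none/minimal, and the share shifting to that category is overstated to that extent.

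This rests on 0 to 3 item coding, on the reading of the gate, and on the gate applying at follow-up as the text implies. How many participants are affected, and what happens to the between-group difference, cannot be determined from the article.

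**What to change.** 1. Confirm from the interview forms whether all nine items were asked at screening, baseline, 4 months and 8 months.
2. Correct the Measures section to state that all nine items are asked of every participant at every assessment. The Discussion says trial procedures are still in progress, so apply this at all remaining 4- and 8-month interviews.
3. Compute the 0 to 27 score and assign bands only from nine administered items.
4. If any follow-up interviews were gated, treat the unasked items as missing, not zero, for example by multiple imputation from the asked items and the participant's other interviews. Add a sensitivity analysis on the sum of the two core items, which exists for everyone. A gated interview never observes the seven items below the gate, so the imputation leans on its model and on interviews given in full; report that limit.

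The cost is a slightly longer interview for those below the gate and some loss of precision for interviews already gated. If all nine items were always asked, the cost is one corrected sentence.

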General procedures include two sequential depression screenings of individuals by senior center staff over two weeks using the Patient Health Questionnaire (PHQ-9). Those eligible (PHQ-9 ≥ 5) and willing provide written consent using an approved Institutional Review Board (IRB) form (Thomas Jefferson University IRB control #06f.551) and receive a baseline home interview conducted by academic partners. Participants are then randomized to receive BTB immediately or 4 months later (wait-list control). All participants are reassessed at 4 and 8 months by academic partners who remain masked to study assignment. The design allows for a true two-group comparison at 4 months to evaluate intervention effects on symptom severity (primary end point), quality of life indicators, anxiety, depression knowledge, and functional disability (secondary endpoints); an evaluation of long-term (8 months) effects for the initial treatment group; and whether wait-list controls derive similar benefits from 4 to 8 months. Treatment fidelity is enhanced through use of treatment manuals, session implementation checklists, audiotaping and rating of randomly selected sessions, one-on-one supervision and bi-weekly group debriefing sessions involving structured case presentations and review of treatment documentation.

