### BTB Intervention

Up to 10 one hour sessions occur over 4 months. A home visit can be replaced with check-in telephone calls once steady progress is demonstrated. Sessions integrate five treatment components previously shown to be effective and modified in BTB to resonate with cultural preferences: case management, referral and linkage, depression education, stress reduction techniques, and behavioral activation. (Table 2) Critical is tailoring to participants' depression knowledge level, care management needs, and self-identified goals and behavioral activation plans.

**Table 2 T2:** Intervention Component, Content, and Modification for Target Population

Component	Content	Modifications for Target Population
Education [14,25]	Education provides foundation for introducing other elements of the intervention. It enhances readiness of individuals to address emotion-laden concerns. Specifically, education was provided on: 1) depressive symptoms, 2) how to talk to doctor about symptoms; and 3) relationship of depression to activity and negative cycle of disengagement	1) Used participant's words and own labeling to describe feelings (e.g., "I am feeling blue"). 2) With rapport and only over time, feelings are then labeled as symptoms of "depression." 3) Discussed how to talk to a doctor of a different race. 4) Withdrawal of activity related to specific activities person identified as valued. 5) Used visual mood rating scales and calendars with big print to minimize vision and literacy challenges.
Care management [12,14]	Care management has been found to be more effective than therapy or medication alone for low income elders for whom financial, functional disability and lack of social resources may contribute to depressive symptoms. Specifically this involved: 1) assessment 2) coordination with other services/care management; 3) problem identification and resolution	1) Considered a wide range of care needs most relevant to this population including home repairs, financial concerns, home and neighborhood safety, family conflict. 2) Housing and neighborhood difficulties were evaluated to determine whether person could remain in setting.

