As to our second aim, we seek to evaluate whether participants in the initial treatment group maintain reduced symptom presentation from 4 to 8 months. We view retention as a one-sided concept such that any beneficial effect of the intervention at four months is improved or at least maintained at 8 months. Lack of retention is then considered a non-trivial loss of benefit. In the language of clinical treatment trials, this is a "clinical equivalence" or "non-inferiority" hypothesis. Thus, our analyses for our second aim will focus on estimating the amount of 4-month benefit that is retained at 8 months for the treatment group only. We will use confidence intervals in reporting results in order to understand how much loss of benefit is consistent with the data we obtain. Given that the main outcome measure, PHQ-9, has cut off points related to DSM IV depression conditions (e.g., dysthymia, major depression), we will be able to evaluate loss of benefit and retention of effect within the treatment group based on clinically relevant features.

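### The 14-item quality-of-daily-life scale rates change over the past month, so it cannot test whether quality-of-life improvements are maintained at 8 months

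*Protocol article*

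**What the plan says.** All of this comes from the protocol article.

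- **The instrument (Measures, Table 1).** Quality of daily life has 14 items: "Adapted from the Perceived Change Index, items reflect mood, sleep quality and daily well-being". They are "rated from 1 (gotten much worse in past month) to stayed the same (3) to improved a lot (5". The midpoint, 3, therefore means no change over the past month.
- **The aim (Aims and study hypotheses).** The secondary aim is to "evaluate whether BTB has immediate (4 months) and long-term (8 months) effects on quality of life indicators", among other outcomes. The expectation is that "improvements will be maintained at 8 months and that the wait-list control group will demonstrate similar improvements at 8 months", the wait-list group having by then been treated.
- **The schedule (Methods/Design; BTB Intervention).** "All participants are reassessed at 4 and 8 months by academic partners". On treatment: "Up to 10 one hour sessions occur over 4 months". In the initial treatment group the months between the 4- and 8-month visits are thus follow-up after treatment.
- **The retention analysis (Analytic plan).** The second aim is handled by "estimating the amount of 4-month benefit that is retained at 8 months for the treatment group only". This text is written for depressive symptoms on the PHQ-9.
- **The other quality-of-life scale (Table 1).** Overall quality of life has 12 items rated from 1 (poor) to 4 (excellent), which is a rating of current state.

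The article does not say that this change-rated scale is treated differently from the scales that measure a state.

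**The concern.** Maintenance is a statement about level: the participant is as well at 8 months as at 4 months. A scale that asks about change in the past month does not record level. Someone who improved during treatment and then held steady has, correctly, stayed the same in the month before the 8-month visit and scores at the midpoint.

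Two things are at stake. First, a fall in this score from 4 to 8 months could be reported as loss of benefit when nothing was lost. Second, a midpoint score at 8 months could be reported as maintenance when the benefit went before the last month. The scale cannot tell these two histories apart, and that is the distinction the hypothesis depends on.

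**Working it through.** The article gives no figure that depends on this point, so there is none to reproduce. The check scores the scale under its own anchors.

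**Inputs from the article:** 14 items; item range 1 to 5; 3 = no change; recall window one month; visits at 4 and 8 months.

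**Assumption for illustration:** the item mean at 4 months. The article gives none, so three values are used.

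**Score range.** Minimum 14 × 1 = 14; neutral 14 × 3 = 42; maximum 14 × 5 = 70.

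**Participant A: improved by 4 months, benefit fully kept, no further change.** Every item is 3 at 8 months, so the total is 14 × 3 = 42.

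| Assumed item mean at 4 months | Total at 4 months | Total at 8 months, benefit fully kept | Apparent fall |
|---|---|---|---|
| 3.8 | 14 × 3.8 = 53.2 | 42 | 11.2 |
| 4 | 14 × 4 = 56 | 42 | 14 |
| 5 | 14 × 5 = 70 | 42 | 28 |

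Apparent retention above neutral is (8-month total − 42) / (4-month total − 42) = 0 in every row, although true retention is 100%. The zero is not an estimate. It follows from the anchors once the participant is stable in the last month, whatever the 4-month gain.

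**Participant B: same gain at 4 months, all of it lost in months 5 to 7, stable in month 8.** Every item is again 3, total 42. A and B have opposite outcomes and the same 8-month score.

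**Could a later analysis recover the missing information?** The 4-month visit covers roughly month 3 to month 4, and the 8-month visit roughly month 7 to month 8. Of the four months between visits, one is observed and three are not. Change ratings therefore cannot be summed to a level at 8 months, however the score is modelled.

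**The 4-month contrast.** Both randomised groups answer the same past-month question at the same visit, so the comparison is valid for what the scale measures. Gains made earlier in treatment and then held score 3, so the contrast reflects recent change, not the whole gain since baseline.

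**The case against.** The strongest reply is that the article never states the analysis that would go wrong. The retention method is written for the PHQ-9, and the article does not say that 4- and 8-month scores on this scale will be subtracted or that a lower score will count as loss. A condensed article may leave the handling of secondary outcomes to the full protocol or the statistical analysis plan, neither of which is shown. This stands as far as it goes: a reader might infer that the plan will misread full retention as loss, but the documents do not commit to that comparison. It does not remove the mismatch. The instrument and the maintenance hypothesis are both fixed in this article, and no analysis of the scale can separate participants A and B.

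A second tempting inference is that the initial group would look worse than the just-treated wait-list group at 8 months despite equal well-being. The documents do not support this as a stated harm. Methods/Design reserves the true between-group comparison for 4 months and describes the 8-month questions group by group; the aims label the 8-month symptom analyses as within-group.

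A third reply is that an 8-month mean of 3 or more could be read as improved or at least maintained. On this scale it shows only that there was no decline in the last month. Participant B would pass.

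Finally, the scale is one of six secondary measures in Table 1, the PHQ-9 primary outcome is untouched, and a level-type quality-of-life scale is already planned. All of that is correct. It limits the importance of the point and makes the remedy easy.

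**Conclusion.** The point holds as a mismatch between an instrument and an aim. The quality-of-daily-life scale cannot test maintenance at 8 months: full retention, and full loss before the last month, both give 42 of 70. If 4- and 8-month scores were compared, full retention would appear as a fall of 11.2, 14 or 28 points for assumed 4-month item means of 3.8, 4 or 5, which is the whole of the gain above neutral each time. The equal scores follow from the printed anchors and assume that participants answer the past-month question as worded. The size of the fall depends on the assumed 4-month mean and on a comparison that the article implies but does not state.

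The conclusion does not extend to the primary outcome, to the overall quality-of-life scale, or to the validity of the 4-month randomised contrast on this scale. It should be corrected before the 8-month secondary results are analysed, but it does not threaten the trial's main result.

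**What to change.** 1. State that differences between 4 and 8 months on the 14-item scale will not be used as evidence of maintenance or of loss.
2. Report the scale at each visit as perceived change over the past month. Describe the 4-month group contrast in those terms. If the 8-month mean is set against 3, say that a mean of 3 or more shows only no decline in the last month, not maintenance.
3. Base the 8-month quality-of-life maintenance claim on the 12-item overall quality-of-life scale, whose 4- and 8-month scores can be compared as levels.

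The cost is a change of wording in the secondary analysis, with no new data. The downside is that one secondary scale no longer supports a maintenance claim. Because the 12-item scale is described by different content (pleasure, hopefulness, relationships), the sleep and daily well-being items of the 14-item scale will have no maintenance result of their own.
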